### Contamination

Noncompliance with the assigned surfacing could occur if schools install a different surface to the one assigned, or install a different surface altogether (eg a fixed rubber surface). Analysis will be by intention to treat amongst randomized schools. Actual surface installed will be recorded for each school by direct observation during a site visit. Because both surfaces are approved, and the project has support from the TDSB, we anticipate that most schools will comply with the results of randomization. In addition, neighbourhood children may use school playground equipment outside school hours. Such use will not affect the results of the trial since data collection is based on incident reports completed during the time school is in session.

### Covariates

School population, playground size, socioeconomic status, and number of hours of play may influence injury rates although such effects would be independent of surfacing so it is simply necessary to balance the groups. The randomization has already been performed and school population, playground size, and socioeconomic status are balanced as would be expected with 37 clusters (see table 1 in sec 2.3). At each school, supervised outdoor play occurs for equal mandated time periods (totaling 2 hours) each day, weather permitting. Intensity of supervision will be addressed by calculating the student to teacher ratio at each school according to the playground supervision roster.

Weather will be the same for all schools, but it is possible that effect modification (different injury risks by surface in wet vs dry weather, or when frozen) could occur. Accordingly, rainfall and snowfall amounts will be recorded from Environment Canada web records and will be used in a secondary analysis as described below.

Depth of undersurface measurements will be done three times per year (September, January and June) of surfaces at all schools at falling points and slide exits. Falling heights will be recorded by surveying the equipment using diagrams and digital photos, and asking parents for the location of any injury fall. Depth measurements and falling heights will be used as covariates in the analyses (see appendix).

## What are the planned inclusion and exclusion criteria?

### Inclusion Criteria – Schools

Schools were eligible for inclusion if they were due for replacement of playground equipment and surfacing in the 2003/2004 school year. Thirty-seven elementary schools (of 365 in total) in the Toronto District School Board met this criterion. These schools are representative in terms of size and socioeconomic status. School principals will give consent for data collection at their school.

### Inclusion Criteria – Students

Any student injured on the playground (with sufficient severity to require an incident report) during school hours is eligible for inclusion. School hours when playgrounds are used include 15 minutes before the morning bell, 15 minutes each of morning and afternoon recess, an hour at lunch time, and 15 minutes after dismissal. During these times, supervision of play is provided at each school. The threshold for completing an OSBIE form is ‘when someone receives medical/dental attention’

### Exclusion Criteria – Students

Although we do not expect them, children with fractures through pathological bone (eg pre-existing tumor, osteoporosis) will be excluded.

## What is the proposed duration of the treatment period?

The TDSB planned the resurfacing of the playgrounds in the spring and summer of 2003, and the randomization was performed then. HSC ethics review board approval was obtained prior to randomization. School playground replacement began in the summer of 2003 with completion at all schools anticipated in the spring of 2004.

## What is the proposed frequency and duration of follow-up?

Data will be collected during two complete school years once funding is received. Data will be collected during supervised school hours (see inclusion criteria for definition).

## What are the proposed primary and secondary outcome measures?

### Primary Outcome Measure - Upper Extremity Fracture Rates

The primary outcome is an upper extremity fracture occurring on the school playground. The definition of an upper extremity fracture will be parental report of a physician’s diagnosis of ‘break’, ‘fracture’, or ‘dislocation’ in children who were x-rayed AND required a cast, splint or sling.

### Secondary Outcome Measure–Overall Playground Injury Rates

School playground injury is defined as any injury requiring completion of an incident report. OSBIE policy states that incident reports are to be filled out ‘when someone receives medical/dental attention’.

### Secondary Outcome Measure – Head Injury Rates

The definition of a head injury (based on parental report) will include children with a physician’s diagnosis of head injury, skull fracture, concussion, or brain injury.

## How will the outcome measures be measured at follow-up?

Ontario School Board Insurance Exchange (OSBIE) incident reports are routinely completed by teachers for any injury (playground or other) in every TDSB school. The threshold for completing an OSBIE form is ‘when someone receives medical/dental attention’. Inservices will be held for teachers at each school to remind them of the forms and the threshold for completion, as a means of standardizing the reporting.

The research assistant will receive new OSBIE incident reports describing playground injuries at each school on a weekly basis.

Parents of children who are injured will be contacted by telephone (after initial contact by letter) for consent and data collection. The CHIRPP form (see appendix) will be completed by telephone, such use has been validated (24). Additional telephone questions added to the CHIRPP form for details on the event and the injury are given in the appendix. The research assistant will work flexible hours allowing evening phone calls to parents where necessary. Hospital for Sick Children language line interpreter services will be used if a parent or caregiver has insufficient English.

To validate the injury data for severe injuries, health records (emergency sheet, and discharge sheet if admitted) will be obtained (with consent) for all children attending an emergency department or admitted to a hospital. ICD 10 diagnostic and procedure codes will be abstracted from emergency and inpatient records by trained coders.

We expect that the OSBIE incident reports will capture all severe injuries especially if there is an absence from school. A small number of injuries may have a delayed presentation (after school hours), and not be reported via the OSBIE incident reports. We expect that the school (ie the principals) would be notified if the injury was severe. Principals will be contacted monthly to ensure that no playground injuries have been missed

## What is the proposed sample size?

37 schools, each with approximately 410 students, will be followed for two years, yielding 30,000 student-years of observations. Sample size determinations for each outcome are provided below.

### Primary Outcome Measure

Based on OSBIE data from 1999-2001 we estimate a baseline arm fracture (lambda zero) rate of 4 per 1000 student years. A clinically significant difference would be a halving of this rate to 2 per 1000 student years (lambda one). This is consistent with reports of sand having ½ to 1/6 the injury rate of other surfaces (14). Each school of 410 students provides 820 student years (y) of data over the two year study. Hayes’ method of sample size estimation for cluster randomization was used (25), where the number of clusters (c) per arm is:

Setting alpha = .05 and power at 80%,and k (coefficient of variation between clusters) at 0.2, we estimate that 17 clusters per arm or 34 schools in total will be required. 37 have been randomized so the study should have ample power. Ample power exists if the coefficient of variation is between 0.1 and 0.3 (see appendix).

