# THE NEED FOR A TRIAL

## What is the problem to be addressed?

We propose a cluster randomized trial to determine which surface (engineered wood fibre or sand) better protects children from upper extremity fractures from school playground falls.

Fully 60 percent of Canadian children’s Emergency Department (ED) injury visits result from sports and leisure activities(1). Playground equipment injuries alone comprise ten percent of ED injury visits among 5 to 9 year old Canadian children (2). At Toronto’s Hospital for Sick Children from 1997 to 2002, 739 upper extremity fractures were seen from playground equipment falls, of which 331 (45%) required operative reduction. By comparison, 353 upper extremity fractures were seen from standing height playground falls, of which 49 (14%) required operative reduction (data source: Canadian Hospitals Injury Reporting and Prevention Program, CHIRPP, unpublished). In the US (3), a prospective cohort study found that playground injuries had a higher severity than any other child injury mechanism except transportation. This study also found that the admission rate (8%) for playground injuries was higher than that for any other child injury mechanism except transportation. Phelan (4) reported 920,000 emergency department visits in the US from 1992 to 1997 resulting from playground equipment falls, and concluded that “interventions targeting schools and 5 to 9 year old children may have the greatest impact on reducing emergency visits for playground injuries.” Chalmers (5), in a study in New Zealand, demonstrated that optimizing falling height and surface conditions would decrease playground injury ED visits by 45%.

The major determinants of playground injury reported consistently in case control studies are fall heights greater than 1.5 metres and poor surfacing. Falls of 1.5 metres and up had 2.0 to 4.1 times higher odds of significant injury than lower falls (5,6). Lack of impact absorbing surfaces increased injury odds 2.3 times in a New Zealand study (5). In Kingston Ontario, injury odds were 18 times higher for a fall onto a surface which did not meet CSA impact absorption standards (7).

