## What are the principal research questions to be addressed?

### Primary research question:

Is there a difference in playground upper extremity fracture rates in schools with Fibar® (wood fibre) surfacing compared to schools with granite sand surfacing?

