## Why is a trial needed now?

Despite the importance of playground injuries, to date, there are no randomized trials of injury countermeasures. Published intervention studies are pre post studies without injury outcomes. Therefore, they cannot be used to guide decision making. By examining injury rates by type of surface, it may be possible to dramatically reduce the numbers and severity of children’s playground injuries. Last, there is a unique opportunity to perform this study within an existing program of playground replacement carried out by the Toronto District School Board. This means that a high quality randomized trial can be conducted with high leverage and modest cost. In the summer of 2000, the Toronto District School Board (TDSB) removed playground equipment that did not comply with newly revised Canadian Standards Association (CSA) standards (20). Subsequently, there has been a phased replacement of equipment. In the spring of 2003, retrofitting and replacement of equipment began in 37 school playgrounds that had partial equipment removal. Both wood (Fibar®) and granite sand surfaces are routinely used in TDSB schools. The Toronto District School Board agreed to randomize surfacing for these 37 schools, allowing an ideal opportunity to determine the relationship between surface type and playground injury rates. The $1.7M cost of replacing the playgrounds according to the randomization schedule was covered by the TDSB. Playground injuries can be identified from a prospectively recorded population based database (Ontario School Board Insurance Exchange - OSBIE). The playgrounds have a service life of 10 to 20 years, so outcomes from this randomized cohort can be assessed once funding is secured.

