### Co-interventions

The playground resurfacing program is part of a larger program that will also bring playground equipment up to CSA standards. Therefore, there may be modification of play structures within playgrounds. Such modifications, however, will be similar and randomizing the intervention will balance such cointerventions. We know that the total cost of replaced equipment is balanced between groups (table 1 in sec. 2.3). Actual equipment present at each playground will be surveyed, photographed, and measured (see appendix). Installation and maintenance of both surfaces will be done by the same TDSB employees working to CSA standards. Maintenance may differ systematically between groups if one surface is more costly or difficult to maintain, so actual surfacing depths will be measured during the followup period and treated as covariates.

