### Secondary Outcome Measure

Based on OSBIE data from 1999-2002, we estimate a baseline injury rate of 15 reported injuries per 1000 student years. Anticipating a 33% reduction in injuries overall, and using the method above, we estimate that 15 clusters per arm or 30 schools in total will be required. 37 schools have been randomized so the study should have ample power, and would potentially be able to detect smaller differences.

Severe head injuries are rare events. They will be recorded because of their importance but we do not anticipate a statistically significant difference because of the small numbers.

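### The claim of ample power rests on a 1999-2001 fracture rate not shown to apply to the Fibar arm, and at k = 0.3 it fails on the protocol's own inputs

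*Protocol*

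**What the plan says.** The primary question in the protocol compares "schools with Fibar® (wood fibre) surfacing compared to schools with granite sand surfacing". The sizing, under *What is the proposed sample size?*, *Primary Outcome Measure*, begins: "Based on OSBIE data from 1999-2001 we estimate a baseline arm fracture (lambda zero) rate of 4 per 1000 student years". It treats a fall to 2 per 1000 as the clinically significant difference. "Each school of 410 students provides 820 student years (y) of data over the two year study". With alpha 0.05, 80% power and k = 0.2, it asks for 17 schools per arm (34 in all), notes that 37 were randomized, and describes power as ample for k anywhere from 0.1 to 0.3, citing an appendix.

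The overall-injury outcome is handled the same way: "Based on OSBIE data from 1999-2002, we estimate a baseline injury rate of 15 reported injuries per 1000 student years". A one-third reduction is said to need 15 schools per arm, and power is again called ample.

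Two other sections bear on where these rates come from. *Why is a trial needed now?* says that in summer 2000 the school board "removed playground equipment that did not comply with newly revised Canadian Standards Association (CSA) standards", and that retrofitting at the 37 trial schools, which had lost part of their equipment, began in spring 2003. *Co-interventions* adds: "The playground resurfacing program is part of a larger program that will also bring playground equipment up to CSA standards".

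**The concern.** The rate given to the higher-risk arm is a historical one. Its window includes a period with non-compliant equipment still in place and a period after that equipment was taken out, and it closes before the trial playgrounds were rebuilt. The protocol does not say which schools, surfaces or equipment it covers, and gives no argument for carrying it over to Fibar on new equipment. Its own background names fall height and surfacing as the main determinants of playground injury, and those are what the programme changes.

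The halving has a similar gap. The source cited for it is described in the background as comparing sand with gravel, grass, mats and asphalt. No wood fibre comparison is reported from it.

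Power for a rate comparison depends on the number of events. The results are meant to feed the next revision of the national playground standard. If fewer fractures occur than planned, a null result from a trial described as amply powered could be taken to show that the two surfaces are equivalent.

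**Working it through.** **Inputs.** Rates of 4 and 2 per 1000, y = 820 student-years per school, k = 0.2 with a range of 0.1 to 0.3, alpha 0.05 and 80% power are all from the primary sample size section. The 37 schools (19 and 18) are from the trial design section and are treated as 18.5 per arm. The formula is not legible in the available copy, so the standard Hayes form for unmatched rates is used, two-sided:

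c = 1 + (z₀.₉₇₅ + z₀.₈₀)² × [(λ₀ + λ₁)/y + k²(λ₀² + λ₁²)] / (λ₀ − λ₁)², with (1.960 + 0.842)² = 7.849.

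**The plan's own figure (k = 0.2).**
- (0.004 + 0.002)/820 = 7.317 × 10⁻⁶
- 0.04 × (0.004² + 0.002²) = 0.800 × 10⁻⁶
- Sum 8.117 × 10⁻⁶; divided by 0.002² this is 2.029
- c = 1 + 7.849 × 2.029 = 16.93, so 17 per arm. The protocol's number reproduces.

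**Power with 37 schools.** Inverting the formula, power = Φ(√[(c − 1)(λ₀ − λ₁)²/V] − 1.960), where V is the bracketed term. With c = 18.5 and k = 0.2: √(17.5 × 4 × 10⁻⁶ / 8.117 × 10⁻⁶) = 2.937, less 1.960 is 0.977, so 83.6%.

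**The upper end of the plan's range (k = 0.3), rates unchanged.**
- The k term becomes 0.09 × 2.0 × 10⁻⁵ = 1.800 × 10⁻⁶, so V = 9.117 × 10⁻⁶
- c = 1 + 7.849 × 2.279 = 18.89, so 19 per arm, or 38 schools
- Power at 18.5 per arm is Φ(2.771 − 1.960) = 79.1%

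**Sensitivity to the baseline rate.** The documents give no rate for Fibar on replaced playgrounds, so the rates other than 4 are assumptions. The halving is kept throughout.

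| Fibar v sand, per 1000 | Schools per arm for 80% (k = 0.2) | Power, k = 0.1 | Power, k = 0.2 | Power, k = 0.3 |
|---|---|---|---|---|
| 5 v 2.5 | 15 | 92.5% | 90.0% | 85.6% |
| 4 v 2 | 17 | 86.2% | 83.6% | 79.1% |
| 3.6 v 1.8 | 19 | 82.6% | 79.9% | 75.6% |
| 3 v 1.5 | 22 | 75.5% | 73.1% | 69.2% |
| 2.2 v 1.1 | 29 | 62.4% | 60.6% | 57.6% |
| 2 v 1 | 32 | 58.4% | 56.7% | 54.1% |

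At k = 0.2, a baseline 10% below the stated one (3.6 instead of 4) uses up the whole margin. Expected fractures are 18.5 × 820 × (0.004 + 0.002) = 91 at 4 v 2, and 68 at 3 v 1.5.

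**Overall injuries, 15 v 10 per 1000.**
- k = 0.2: V = 0.025/820 + 0.04 × 3.25 × 10⁻⁴ = 4.349 × 10⁻⁵; c = 1 + 7.849 × 4.349/2.5 = 14.65, so 15 per arm as stated; power 89%.
- k = 0.3: V = 5.974 × 10⁻⁵; c = 19.75, so 20 per arm; power 77%.

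**The case against.** The strongest reply is that nothing in the calculation is wrong, and that the documents do not show the rate to be too high. Both points stand.

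- **Surface mix.** A reader might infer that the 4 per 1000 excludes wood fibre. The documents do not support that. Both surfaces are said to be in routine use in the board's schools, so the data may include Fibar playgrounds. The rate is only not shown to be specific to them.
- **Direction.** A reader might infer that compliant equipment must lower the rate. Other features point upward. Part of the window had less equipment to fall from; the background reports bark with fracture rates at least as high as concrete; and in-services and monthly calls to principals may raise capture above routine reporting. If 4 per 1000 were the average of the two arms (5.33 v 2.67), power would be about 92%.
- **Size.** The background cites a New Zealand study that "demonstrated that optimizing falling height and surface conditions would decrease playground injury ED visits by 45" per cent, and 4 × 0.55 = 2.2 gives 61% power. That figure concerns emergency visits in another country and optimized conditions, not CSA compliance or school-reported fractures. Part of the baseline window already follows the equipment removal. Some playground fractures are standing-height falls: 353 of 1,092 (739 + 353) in the hospital series quoted. If that split applied (an assumption), a 45% cut in equipment falls alone would lower the total by about 30%, to 2.8 per 1000, with about 70% power. So 61% is one end of a range, not an estimate.
- **The halving.** The protocol offers it as a clinically significant difference, merely consistent with reports on other surfaces. It does not claim that the source tested wood fibre.

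All 37 eligible schools are already randomized, so the design would not change. That limits the consequence to what is claimed about power. It does not make the claim correct.

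**Conclusion.** The concern holds in a limited form: the unqualified statement of ample power is not supported. This rests on two grounds.

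The first needs no assumption about the baseline. At k = 0.3, inside the range the protocol calls ample, its own rates require 38 schools, and the 37 available give 79%, just short of the 80% target. The cited appendix is not in the available document, so any further working there could not be checked.

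The second is that the claim depends on one rate of undescribed origin, with little room for error. At k = 0.2, power runs from 90% at 5 per 1000 to 57% at 2, and 80% is lost just above 3.6. These figures assume the halving, 820 student-years per school and the Hayes formula.

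Two stronger conclusions do not follow: that the trial is underpowered, or that the sample size was miscalculated. The direction of error in the baseline is unknown, and the 17 per arm is right for the inputs given.

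**What to change.** In both sample size subsections:

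1. State which schools, surfaces and equipment lie behind the 4 and the 15 per 1000, noting that the windows differ (1999-2001 and 1999-2002).
2. If they can be extracted, base the comparator rates on incident reports from board schools that already have Fibar on replaced playgrounds. The protocol calls Fibar the most popular surfacing for newly replaced Toronto school playgrounds, but does not say whether reports can be sorted by surface.
3. If they cannot, replace the word ample with power for the 37 schools over a two-sided range of baseline rates, for example 2 to 5 per 1000, crossed with k of 0.1 to 0.3, as in the table above. Do the same around 15 per 1000 for overall injuries.
4. Say that the source cited for the halving is reported in the background without a wood fibre comparison.

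The cost is at most one data extract and some rewording, with a less favourable stated power. An extract may be imprecise, so the range is worth showing in either case. No extra schools are needed.

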## What is the allocation method?

A computer generated random number list was used to assign the 37 participating schools to Fibar® or granite sand groups. School level covariates including student population, socioeconomic status, and playground size are balanced between the groups as shown in table 1 below:

Table 1: Results of Randomization:

|  | **Fibar Schools**  **N = 19**  **Mean (S.D.)** | **Granitic Sand Schools**  **N = 18**  **Mean (S.D.)** | **P-Value** |
| --- | --- | --- | --- |
| Number of Students | 409.2 (312.1) | 416.3 (195.4) | 0.934 |
| Learning Opportunities Index (LOI) | 0.55 (0.27) | 0.49 (0.29) | 0.533 |
| Size of Playground (m2) | 18826.6 (22657.1) | 17142.8(22589.3) | 0.835 |
| TDSB Budget ($) | 42914.6 (31086.8) | 48658.70 (27426.2) | 0.555 |
| Cost of re-surfacing ($) | 7073.68 (1442.55) | 5688.9 (1179.9) | 0.003 |

Note: The TDSB Learning Opportunities Index 2002-03 combines information from the following variables: average and median income of families with school-aged children; parental education; proportion of lone-parent families; recent immigration; housing type (apartment, single detached housing); student mobility. It is the standard socioeconomic status measure for TDSB schools.

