## What is the planned recruitment rate?

All schools will be recruited at the beginning of the trial and we anticipate that all schools will agree to participate. Our previous work with OSBIE data suggests 15 playground injuries per 1000 students per year. Approximately 225 playground injuries per year will occur among 15,000 students, or 23 per month across the ten months school is in session. We believe that 90% of parents of injured children will agree to participate as there is only a minor inconvenience (one phone call) associated with participation and we have achieved this rate of participation in a previous telephone survey of play equipment injuries in Toronto (26).

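### Ample power is claimed up to a between-school coefficient of variation of 0.3, but the 37 schools give about 79% there, and about 76% if 90% of parents take part

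*Protocol*

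**What the plan says.** The sample size section of the Protocol (Primary Outcome Measure) starts from "we estimate a baseline arm fracture (lambda zero) rate of 4 per 1000 student years" and takes a halving to 2 per 1000 as the difference worth detecting. With 820 student-years per school, alpha 0.05, 80% power and k = 0.2, Hayes' method for cluster trials gives 17 schools per arm, 34 in total. The section then says that "37 have been randomized so the study should have ample power", and widens the claim: "Ample power exists if the coefficient of variation is between 0.1 and 0.3 (see appendix".

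Three other sections bear on this:
- The trial design section gives the allocation as 19 wood fibre and 18 sand schools.
- The primary outcome section defines an upper extremity fracture through the parent's report of a physician's diagnosis. The follow-up section says that this report is obtained by telephone, with consent.
- The recruitment section states "We believe that 90% of parents of injured children will agree to participate". The sample size section makes no allowance for the remaining 10%.

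**The concern.** The protocol's case for ample power is that the schools randomised outnumber the schools required: 37 against 34. That comparison is made at k = 0.2 and then extended to k = 0.3 without a figure in the main text. Required numbers rise with k, so the margin of three schools may be used up before 0.3. Fractures that cannot be counted because a parent declines would use up more of it.

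The results are meant to inform a national playground standard. If the trial finds no significant difference, a reader told that power was ample across this range may take the result as stronger evidence of equivalence than the design can give.

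**Working it through.** **Inputs.** From the sample size section: λ0 = 0.004 and λ1 = 0.002 per student-year, y = 820 student-years per school, alpha 0.05, power 80%, k = 0.2, with a claimed range of 0.1 to 0.3. From the trial design section: 19 and 18 schools. From the recruitment section: 90% participation.

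**Formula.** The displayed equation is missing from the copy reviewed. The form used is

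c = 1 + (z₁ + z₂)² × [(λ0 + λ1)/y + k²(λ0² + λ1²)] / (λ0 − λ1)²,

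with z₁ = 1.960 and z₂ = 0.842, so (z₁ + z₂)² = 7.849.

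**Reproducing the plan's figures.** At k = 0.2:
- (λ0 + λ1)/y = 0.006/820 = 7.317 × 10⁻⁶
- k²(λ0² + λ1²) = 0.04 × 2.0 × 10⁻⁵ = 0.800 × 10⁻⁶
- c = 1 + 7.849 × 8.117 × 10⁻⁶ / 4.0 × 10⁻⁶ = 16.93, so 17 per arm and 34 schools, as stated.

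The protocol does not say whether alpha is one- or two-sided. A one-sided test gives 13.55 (14 per arm), and dropping the leading 1 gives 15.93 (16 per arm), so only the two-sided form with the leading 1 returns 17. The same form gives 14.65 (15 per arm) for the secondary outcome at 15 v 10 per 1000, which also matches the protocol.

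**Schools required at k = 0.3.** The second term becomes 0.09 × 2.0 × 10⁻⁵ = 1.800 × 10⁻⁶, and c = 1 + 7.849 × 9.117/4.0 = 18.89. That is 19 per arm, 38 schools.

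**Schools required at 90% participation.** The countable rates become 0.9 × 4 = 3.6 and 0.9 × 2 = 1.8 per 1000. Then (λ0 + λ1)/y = 6.585 × 10⁻⁶, λ0² + λ1² = 1.62 × 10⁻⁵ and (λ0 − λ1)² = 3.24 × 10⁻⁶.
- k = 0.2: c = 1 + 7.849 × 7.233/3.24 = 18.52
- k = 0.3: c = 1 + 7.849 × 8.043/3.24 = 20.49, so 21 per arm, 42 schools.

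**Power with the schools allocated.** Power = Φ(|λ0 − λ1|/SE − 1.96), where SE² is the sum over the two arms of (λ/y + k²λ²)/(n − 1). The higher rate is placed in the 19 wood fibre schools and the lower in the 18 sand schools.

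Example, k = 0.3 with full ascertainment: SE² = 6.318 × 10⁻⁶/18 + 2.799 × 10⁻⁶/17 = 5.157 × 10⁻⁷, SE = 7.181 × 10⁻⁴, and Φ(2.785 − 1.960) = 79.5%.

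| Ascertainment | k | Unrounded c per arm | Power, 19/18 | Power, 18.5 per arm |
|---|---|---|---|---|
| 100% | 0.1 | 15.75 | 86.6% | 86.3% |
| 100% | 0.2 | 16.93 | 83.9% | 83.6% |
| 100% | 0.3 | 18.89 | 79.5% | 79.1% |
| 90% | 0.1 | 17.35 | 82.9% | 82.6% |
| 90% | 0.2 | 18.52 | 80.3% | 80.0% |
| 90% | 0.3 | 20.49 | 76.1% | 75.7% |

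With full ascertainment and the 19/18 split, power stays at or above 80% up to k of about 0.29.

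**The case against.** The strongest reply is that the shortfall at k = 0.3 is one school and less than one percentage point of power, at the edge of a sensitivity range, while the plan's actual calculation is correct. That stands: this is an overstated margin and not an arithmetic error in the stated 17 per arm. It does not rescue the sentence, because a design that only just reaches its target cannot also be described as having power to spare.

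The appendix cited for the range of k is not available, and the protocol does not define what it means by ample. That also stands. But the visible argument compares schools randomised with schools required, and at k = 0.3 that comparison goes the other way.

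The 90% figure may be offset. In-services on the reporting threshold and monthly contact with principals could raise capture above the historical rate. The documents do not say how fractures were identified in the historical data. The 90% rows are therefore a sensitivity analysis on the protocol's own expectation, not a forecast.

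A reader might go further in two directions that the documents do not support:
- **Unequal school sizes.** Table 1 shows that school sizes vary widely, while the calculation assumes equal schools. The loss depends on the size distribution and on how the analysis weights schools. Table 1 gives only means and standard deviations, so no firm figure can be attached.
- **Baseline rate.** The planning rate comes from 1999-2001, and in summer 2000 the board "removed playground equipment that did not comply with newly revised Canadian Standards Association (CSA) standards". A reader might infer that the rate is too high for the new playgrounds. Older equipment could have raised it, but having less equipment could have lowered it, so the direction is unknown.

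**Conclusion.** The claim of ample power holds near the planning value and not across the stated range. With full ascertainment, power is about 84% at k = 0.2 and about 79% at k = 0.3, where 38 schools would be required. Taking the protocol's 90% participation into account, it is about 80% and 76%, and 42 schools would be required at k = 0.3. Only that last combination is a material loss.

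Two inferences would be too strong. The trial is not without reserve, since it has almost four points above target at k = 0.2 with full ascertainment. Nor does 90% participation alone leave it short: 2 × 18.52 = 37.05 schools becomes 38 only when each arm is rounded up, and the actual split gives 80.3%.

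The figures assume a two-sided alpha, equal schools of 820 student-years, and the higher rate in the wood fibre arm. The 90% figures also assume equal refusal in both arms, removing 10% of countable fractures, and a 4 per 1000 rate that is not already net of refusal.

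**What to change.** In the sample size section for the primary outcome, replace the two sentences claiming ample power with power for the 19 and 18 schools actually allocated: about 84% (k = 0.2) and 79% (k = 0.3) with full ascertainment, and about 80% and 76% at 90% participation. State the assumptions behind the 90% figures. Give 38 schools as the requirement at k = 0.3, and 42 at k = 0.3 with 90% participation. Limit any claim of reserve to k of about 0.2 or below with near-complete ascertainment.

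The cost is a rewritten paragraph. No school is added, and data collection and analysis do not change.
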